### Evaluation tool

#### The room & chart audit/observation tool

The audit/observational tool was designed to capture data regarding best practice nursing care of older patients with CI, particularly care processes relating to delirium prevention and management. The tool was informed by key Australian guidelines and documents [12, 23], and was initially developed by the lead author (CT) and subsequently revised by the research team until consensus regarding the included items was reached. Most items require an objective Yes/No/Not applicable answer.

#### Procedure for collecting evaluative data

The audits/observations will be completed by two Research Nurses who will be seconded from other hospital wards at the IH (and hence will be familiar with the hospital and its processes), to work on the project. They will be trained to use the tool by CT, and practice cases will be completed (not for inclusion in the final dataset) until an inter-rater agreement of 90% is achieved [32]. The same two nurses will collect the data on each occasion.

The audits/observations will be undertaken for one full day in each of the six intervention and two control wards on each of the five data collection occasions (i.e., a total of 40 days). The data collection is scheduled to occur over the second half of the month on each occasion, and the specific ward to be audited for the day will be randomly selected, using SPSS’s randomization function. One week prior to data collection, each ward’s Nurse Unit Manager will be informed via email, of the day their ward will be scheduled for data collection.

On each audit morning, the Research Manager (CT) will identify all patients with a documented diagnosis of dementia or delirium, or report of confusion, memory problems or other CI in the patient’s chart, or reported verbally by the Charge Nurse. While it is acknowledged that a formal assessment process would be required to be completely confident that all patients with CI are included, this method described is considered adequate for this study. Moreover, the inclusion of patients identified by a nurse with first-hand knowledge of the patients as likely having CI, will overcome some of the under-reporting of dementia in hospital records [8].

A maximum of eight patients will be selected per day, and allocated equally to each Research Nurse. Where more than 8 patients are identified on a particular day, eight patients will be selected using a commercially available random number generator (42 Random Number) APP downloaded onto an Android smart phone. Each patient will be audited/observed on four separate occasions throughout the day: early morning (7 am–9.30 am), late morning (9.30 am–12.00 noon), early afternoon (12.00 noon–1.30 pm) and mid-afternoon (1:30 pm–3:00 pm). The Research Nurse will be required to remain in the patient’s room for at least 15 min per observation and at least one meal-time will be observed. Research Nurses will be instructed to conduct the observations as unobtrusively as possible, and to be polite if patients speak to them but not to encourage conversation.

As no personally identifying information will be recorded for either nurse or patient, obtaining individual informed consent from each participant is not required by the relevant Ethics Committees. Hence, the participation rate is expected to be very high and patients will be excluded only if the patient is likely to be absent from their room for much of the observation period (e.g., a procedure is scheduled).

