### Context and leadership engagement

The implementation of multi-component evidence–based non-pharmacological practices is being progressed in a large tertiary referral hospital - the Intervention Hospital (IH), located in in South-East Queensland, Australia where two of the study’s Chief Investigators (AH, FG) work. Implementation is across four medical and two surgical wards.

Adequate resources and support are available for the project via an Australian Government grant that allows project staff to dedicate sufficient time to assist hospital staff implement and evaluate activities. Executive level support for the project has been obtained by the establishment of a Steering Committee at project commencement. Key hospital staff, including the Director of Internal Medicine, the Directors of Nursing (Medicine, Surgery), and the Nurse Managers from each IH ward are all members (all accepted the invitation) of the Steering Committee. A consumer representative has also been invited to become a member of the Committee via the Consumer Directed Research Network. The purpose of the Committee is to provide support and guidance regarding the project’s implementation. Where appropriate, Steering Committee members may also be asked to assist with managing organizational processes to facilitate project activities (e.g., rostering of CogChamps to attend workshops, and the inclusion of CI project updates in regular ward meeting agendas).

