### Processes to facilitate changed practices to promote high quality care for patients with CI

#### Recruiting CogChamps

CogChamps are nurses recruited to champion best practice care for older patients with CI (dementia and delirium) in hospital, and a new cohort has been identified for this project. In the first instance, experienced nursing staff from each of the six IH wards who were willing to become Cognition Champions (CogChamps), were identified. CogChamps were required to have over two years clinical experience and (a) a specific interest in dementia and delirium, or (b) have leadership skills. The identification process was a collaborative venture between the nurse unit managers and the research team. CogChamps will be provided with comprehensive dementia and delirium education and training (Workshop 1) and education about necessary leadership and change management skills (Workshop 2), to facilitate changing care practices.

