### Evaluation of implementation activities

The impact and effectiveness of the intervention at the IH will be assessed by comparing the uptake of best practices at this site with another comparable site, located nearby (approximately 10 km away). Two wards (one medical, one surgical) in this hospital will serve as control wards (Control Hospital; CH), and the two hospitals are comparable insofar as nursing staff have been exposed to the same educational modules for dementia and delirium as IH nurses and they have similar patient profiles.

The same data will be collected at both sites.

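### A week's notice of the exact audit day lets wards prepare for the observed-care items; it biases the hospital comparison only if preparation grows more at the intervention hospital than at the control hospital

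*Protocol article*

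**What the plan says.** All references are to the protocol article.

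- **Random draw.** Under Procedure for collecting evaluative data, audits fall in the second half of the month and "the specific ward to be audited for the day will be randomly selected, using SPSS’s randomization function".
- **Notice.** The same section then says that, a week ahead, the Nurse Unit Manager of each ward "will be informed via email, of the day their ward will be scheduled for data collection". The wording covers every ward, so CH managers are told as well, and no occasion is exempted.
- **Amount of observation.** Each of the six IH and two CH wards is audited for one full day per occasion, with at most eight patients per day, each observed four times between 7 am and 3 pm.
- **Use of the data.** Under Evaluation of implementation activities, effectiveness is to be judged by "comparing the uptake of best practices at this site with another comparable site".
- **IH managers' role.** Under Context and leadership engagement, "the Nurse Managers from each IH ward are all members (all accepted the invitation) of the Steering Committee", and "The purpose of the Committee is to provide support and guidance regarding the project’s implementation". Under Recruiting CogChamps, "The identification process was a collaborative venture between the nurse unit managers and the research team". No similar role is described for CH managers.
- **Limitations.** The section on strengths and weaknesses does not mention the notice.

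**The concern.** A random audit day is useful partly because the ward cannot foresee it. Once the day is announced, that part is lost, and one prepared shift can be the whole measurement for that ward on that occasion. Several directly observed items in Table 2 can be improved for a known day: a clock showing the right time, help with meals, re-orienting a confused patient, and what the patient is doing when the observer enters.

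The Discussion presents the direct observations as direct evidence of practice change. If they partly reflect performance on announced days, they say less about routine care. For the comparison between hospitals, the question is whether IH wards might come to use the notice more than CH wards as the project proceeds. If so, part of an apparent gain in uptake would be preparation.

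**Working it through.** **1. The plan's own figure.** (6 IH + 2 CH wards) × 1 day × 5 occasions = 40 audit days, as stated. Table 2 lists four occasions for these audits, which would give 8 × 4 = 32; nothing below depends on which count is right.

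**2. When notice biases the comparison of change.** Let *a* be the rise in item compliance, in percentage points, caused by preparing for an announced day. With no true effect,

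bias in the difference in change = (a_IH,post − a_IH,base) − (a_CH,post − a_CH,base).

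The documents give no value for *a*, so every value below is an assumption.

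| IH base | CH base | IH post | CH post | Bias in difference in change |
|---|---|---|---|---|
| 10 | 10 | 10 | 10 | (10−10) − (10−10) = 0 |
| 0 | 0 | 10 | 10 | (10−0) − (10−0) = 0 |
| 10 | 5 | 10 | 5 | (10−10) − (5−5) = 0 |
| 5 | 5 | 10 | 5 | (10−5) − (5−5) = +5 |
| 5 | 5 | 15 | 5 | (15−5) − (5−5) = +10 |
| 0 | 0 | 20 | 5 | (20−0) − (5−0) = +15 |

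The first three rows cover equal preparation, equal growth, and a constant difference between hospitals. All cancel. Only faster growth at IH gives a positive bias.

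**3. Scale against sampling error.** The maximum sample per occasion is 6 × 8 = 48 patients at IH and 2 × 8 = 16 at CH. For an item at 50%:

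- Standard error of the IH-CH difference on one occasion = √[0.25 × (1/48 + 1/16)] = 0.144, or 14.4 points.
- The argument concerns change from baseline. With independent samples of the same size on two occasions, the standard error is 14.4 × √2 = 20.4 points.
- Biases of 5, 10 and 15 points are then 5/20.4 = 0.25, 10/20.4 = 0.49 and 15/20.4 = 0.74 standard errors.

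This ignores clustering by ward, which with only two control wards would probably enlarge the standard error and lower these ratios.

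**4. What changes after baseline.** Table 1 places both the Steering Committee and the CogChamp nominations at project commencement, listed before the baseline audit. Those ties are therefore already present at baseline. The workshops, Action Plans and facilitators come later and only at IH. Any growth in preparation would have to come mainly from these.

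**5. Which outcomes are exposed.** The directly observed items are. Falls and antipsychotic data taken from the hospital database are largely not. The item on documented cognitive assessment within 24 hours of admission can be changed mainly for patients admitted after the email, so it is only partly exposed.

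**The case against.** The strongest reply is that the notice is symmetric: CH managers receive the same email, and baseline audits appear to be announced too. The IH managers' ties to the project predate baseline, so a constant incentive subtracts out. All of this stands. It limits the point to growth in preparation at IH relative to CH. Such growth is not assured either: if routine care at IH truly improves, there is less left to put right on an announced day.

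A reader might infer that the notice undoes the randomisation. The text does not support that. The draw still stops the research team from choosing favourable days or a favourable ward order, and the protocol never claims that audits are unannounced. What is lost is unpredictability for the wards.

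A reader might also infer that the committee seats show a bias in favour of IH. They show a stake in the project, not that any ward prepares more as time goes on. The committee is described under the title Nurse Managers and the notice goes to Nurse Unit Managers; treating these as one role is reasonable but not stated.

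Finally, observers stay in the room for at least 15 minutes at a time, so staff can react to them with or without notice. That also stands, but reacting to an observer is not the same as a week in which to prepare or to adjust rosters.

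**Conclusion.** The procedure fixes a rule that invites avoidable preparation for the directly observed items, and the limitations do not acknowledge it. The documents support saying that announced days may not represent routine care, and that the IH-CH comparison of change would favour the intervention if preparation grew more at IH than at CH. They do not show that this happens.

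The size cannot be derived from the documents. Under the assumed values it runs from 0 to 15 points, or 0 to about 0.74 of a change-from-baseline standard error before clustering, and zero is a real possibility. If a differential did exist, repeating announced audits would reduce random error but not remove it. This is a worthwhile and inexpensive improvement to the audit procedure; it does not invalidate the evaluation.

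**What to change.** Tell all eight managers only that the audit will fall in the half-month window that is already fixed. Keep the randomised order within the research team, and reveal the ward on the audit morning, when the Research Manager already takes the Charge Nurse's report. Hold one or two reserve days per window; eight ward-days leave room for them. Apply this identically at both hospitals, from baseline if possible. If audits have already been done with notice, report the occasion of the switch.

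The cost is a short change of procedure, occasional rescheduling, and a check that neither site access nor the ethics approvals depend on the notice, since the article does not say why it is given. The change removes advance preparation for a known day. It does not remove reactivity once observers are present, and wards can narrow the remaining days as others are completed.

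If notice must stay, list it as a limitation of the observed-care outcomes, and say that the falls and antipsychotic data from the hospital database are largely unaffected.

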## Background

Cognitive impairment (CI) including dementia and delirium are common amongst older people admitted to acute hospitals [1–3]. Patients with these conditions have a significantly increased risk of serious adverse outcomes when hospitalized, compared with same-aged patients without CI. For instance, dementia is a key risk factor for the development of delirium (patients with dementia have a five to six-fold increased risk of developing delirium than other patients of the same age), which is associated with high morbidity and mortality in older people [4]. Other adverse outcomes associated with both dementia and delirium include cognitive and functional decline, medical and surgical complications, significantly increased risk of falls and longer hospital stays and greatly increased hospital costs [2, 4, 5].

Despite their high prevalence and associated adverse outcomes, dementia and delirium are frequently not recognized or recorded in acute hospitals with delirium being missed in as many as 75% of cases [6–9]. Consequently, appropriate prevention and management strategies [6, 8], are not implemented, which effectively prevent delirium in many at-risk patients [4, 10]. An important reason for the under-recognition of delirium is that nurses working in acute hospitals do not receive adequate or appropriate education in identifying and caring for patients with CI [1, 11]. Accordingly, addressing this issue and ensuring that staff are knowledgeable and adequately skilled to identify and care for these patients has been identified as a key strategy for improving these patients’ care [1, 11–15].

Currently, however, the most effective way of educating staff and initiating practice change for older patients with CI in the hospital environment is unclear, as limited research has been undertaken in this area. Of the studies that have been reported, results generally indicate that, while education can improve knowledge of dementia [13, 16], and delirium [17], education in isolation has little effect on clinical practice [18]. By comparison, the use of knowledge translation principles has been shown to be more effective in producing practice change and preventing delirium [10, 18, 19], and are recommended [20, 21].

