Increased proportion of older patients who are routinely assessed for CI at admission to the hospital.	Room & Chart Audit/Observation tool These data will be collected on multiple occasions throughout the project – (1) Pre- intervention, (2) Following the CogChamps training, (3) Following the implementation of ward specific Action Plans, and (4) Three months following withdrawal of the research team.	The room & chart audit/observation tool included an item regarding cognitive assessment – ‘There is documentation that the patient’s cognitive function was assessed using a standardized assessment tool within 24 h of admission to the ward’. This item was adapted from a similar item developed by Schnitker and colleagues for use in the hospital Emergency Department [38].
Increased implementation of best practice guideline for delirium prevention, management and treatment.	Audits of patient rooms and charts. These data will be collected on the same four occasions as the previous item. Direct observations of Nurse: patient interactions.	The room & chart audit/observation tool includes questions relating to cognitive assessment, pain assessment and management (e.g., Was a pain assessment undertaken? Had analgesia been administered within the last 24 h?), and antipsychotic/benzodiazepine use (Was the patient prescribed or administered any PRN antipsychotic/benzodiazepine medication within the past 24 h?). Items requiring direct observation include aspects of the environment (e.g., Was there a clock set to the correct time, that the patient could see from his/her bed?); nutrition (Was adequate assistance provided to the patient if the patient had difficulty eating or drinking); restraint use (Was the patient restrained?); use of indwelling catheters (IDC; Did the patient have an IDC in situ?), communication (If the patient exhibited confusion/dis-orientation, did the nurse say anything to re-orient the patient?), and patient activity (What was the patient doing when you entered the room?).
Older patients with CI will have fewer adverse outcomes.	Data regarding adverse outcomes from the hospital’s administrative database will be extracted at each data collection point and compared across data collection points and between the IH and CH.	Data regarding falls and antipsychotic use will be obtained from the hospital’s database.

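### The admission-assessment outcome is defined for older patients but scored only on patients already recognised as cognitively impaired, leaving it and the care-process items open to differential ascertainment bias of unknown direction

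*Protocol article*

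**What the plan says.** **Who is audited.** Under Procedure for collecting evaluative data, the Research Manager will "identify all patients with a documented diagnosis of dementia or delirium, or report of confusion, memory problems or other CI". Two sources count: what is written in the notes, and what the nurse in charge says on the day. Up to eight of those identified are audited per ward-day, chosen at random if there are more. The section concedes that only a formal assessment could give full confidence that every patient with CI is included, but states that "this method described is considered adequate for this study".

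**What is measured.** Table 2 (Expected outcomes and project evaluation) names the outcome as "Increased proportion of older patients who are routinely assessed for CI at admission to the hospital". Its audit item is "documentation that the patient’s cognitive function was assessed using a standardized assessment tool within 24 h of admission to the ward". The best-practice items that follow (pain, restraint, catheters, orientation and so on) come from the same audits: "These data will be collected on the same four occasions as the previous item".

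**What the intervention changes.** The champions are trained in the Confusion Assessment Method (Educating CogChamps). The novice facilitators help ward nurses with bedside CI assessments (Enabling CogChamps). Routine discussion of CI at hand-over is given as an example of embedded practice (Sustainability). More intervention-hospital nurses proficient in assessing and documenting dementia and delirium is an expected outcome. The control wards supply the comparison under the same audit procedure (Evaluation of implementation activities).

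**Baseline recognition.** The Background states that "dementia and delirium are frequently not recognized or recorded in acute hospitals with delirium being missed in as many as 75% of cases".

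**The concern.** There are two separate problems.

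1. **The denominator does not fit the outcome.** Screening at admission is done before anyone knows whether the patient has CI. Patients who were screened and found unimpaired are not in the audit unless some other report of CI brings them in, and neither are unscreened patients whose CI went unnoticed. A sample of recognised cases does not estimate the proportion of older patients screened, and this holds whatever is assumed about bias.

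2. **Entry to the sample depends on something the intervention is meant to change.** A charted positive assessment can make a patient eligible and also score yes on the screening item. Better charting opens the chart route, and more talk of CI on the ward opens the Charge Nurse route. If this happens at the intervention hospital and not at the control hospital, the comparison between them does not cancel it. The care-process items share the exposure, because the kind of patient audited may shift as recognition improves.

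At stake is whether a gain, or the lack of one, on these items can be read as a change in practice.

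**Working it through.** The article gives no screening rate, sample size or power for these items, so there is no figure of the plan's own to reproduce. The calculation below is an illustration.

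**Inputs**
- *s*: true share of CI patients with a charted standardised assessment within 24 h. Not in the article; assumed.
- *a*: probability that a screened CI patient is identified for the audit. Assumed 0.9 unless stated.
- *b*: probability that an unscreened CI patient is identified. Taken as 0.25 at the low end, from the Background's figure of up to 75% missed, and 0.50 as a higher value. The 75% is an upper limit and concerns delirium only, so 0.25 is an extreme and not an estimate.

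**Formula.** Share screened among identified CI patients = *a·s* / [*a·s* + *b·(1 − s)*]. For *s* strictly between 0 and 1, this equals *s* only if *a* = *b*.

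**Worked cases**
- *s* = 0.10, *a* = 0.9, *b* = 0.25: 0.09 / (0.09 + 0.225) = 28.6%
- *s* = 0.20, *a* = 0.9, *b* = 0.25: 0.18 / (0.18 + 0.20) = 47.4%
- *s* = 0.20, *a* = 0.9, *b* = 0.50: 0.18 / (0.18 + 0.40) = 31.0%

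**Results** (changes in percentage points, from unrounded shares)

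| Assumption | True share | Audited share | True change | Audited change |
|---|---|---|---|---|
| *a* = *b*, constant | 10% to 20% | 10% to 20% | 10 | 10 |
| *a* 0.9, *b* 0.25, constant | 10% to 20% | 28.6% to 47.4% | 10 | 18.8 |
| *a* 0.9, *b* 0.50, constant | 10% to 20% | 16.7% to 31.0% | 10 | 14.4 |
| *a* 0.9, *b* rising 0.25 to 0.50 | 10% to 20% | 28.6% to 31.0% | 10 | 2.5 |
| *a* 0.9, *b* 0.25, constant | 50% to 80% | 78.3% to 93.5% | 30 | 15.2 |
| *a* 0.9, *b* rising 0.25 to 0.50 | 10%, no change | 28.6% to 16.7% | 0 | −11.9 |
| *a* rising 0.6 to 0.9, *b* 0.25 | 10%, no change | 21.1% to 28.6% | 0 | +7.5 |

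The distortion can go either way. It inflates the gain when identification depends on screening, stays constant and baseline screening is low. It shrinks the gain when recognition of unscreened patients improves, or when baseline screening is high. These figures concern CI patients only; the older patients without CI whom Table 2 also covers are a further mismatch.

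**Care-process items.** Assume that half of CI patients are overt cases and half subtle, that recognition rises from 0.4 (overt) and 0.1 (subtle) to 0.9 and 0.7, and that care within each group does not change.
- Overt share of the sample before: 0.5 × 0.4 / (0.5 × 0.4 + 0.5 × 0.1) = 80%
- Overt share after: 0.5 × 0.9 / (0.5 × 0.9 + 0.5 × 0.7) = 56.25%
- Item met in 30% of overt and 60% of subtle cases: 0.80 × 30 + 0.20 × 60 = 36% before; 0.5625 × 30 + 0.4375 × 60 = 43% after
- Rates reversed: 54% before, 47% after
- Equal rates in both groups: no movement

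**The case against.** The strongest reply is that the plan already admits incomplete case-finding, applies one procedure at both hospitals, and adds the Charge Nurse's report partly to offset under-recording. Nurses at both sites have had the same earlier education. Knowledge, confidence, observed proficiency, and falls and antipsychotic data from the hospital database do not use this sample, and the article names no primary outcome.

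Part of this stands. The other outcomes are untouched, and the identification rule is broad enough that 25% identification of unscreened patients is not a likely value. But the plan's caveat covers only incomplete identification, not identification that changes over time at one hospital. Shared earlier education speaks to comparability at baseline, not after the intervention starts. Random choice of eight patients comes after identification and cannot repair it.

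Three stronger readings are tempting, and the documents do not support them:

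- **That the screening gain will be overstated.** This holds only under some assumptions. The same formula gives understatement when recognition of unscreened patients rises, which is what the intervention might well produce.
- **That the intervention hospital's sample will move from overt to milder cases.** Nothing in the article says so. Some items, such as a visible clock, need not vary with severity at all.
- **That the absence of an age limit from the selection rule is an error.** The article condenses a fuller protocol, where a cut-off may stand, and it describes the tool as meant for older patients with CI.

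**Conclusion.** The point holds in two parts. The mismatch between the stated population (older patients at admission) and the audited one (patients already charted or reported as having CI) follows from the text and needs no assumption. Beyond that, the screening item and the care-process items are open to differential ascertainment bias by time and hospital, because the intervention is aimed at the recognition and documentation that govern entry to the sample.

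Neither size nor direction can be determined from the documents. With screened patients identified at 0.9, a true 10-point gain could appear as about 19 points or about 2.5, depending on whether identification of unscreened patients stays at 0.25 or rises to 0.50. There is no bias in the screening share among CI patients if identification is unrelated to screening, and none in a care item that does not vary with how evident the CI is. These items should not be called biased in a known direction; as designed, a gain or a null result on them would be hard to interpret.

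Analysis alone is unlikely to repair this, since the article describes no record of the patients who were not identified.

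**What to change.** 1. **Admission-assessment item.** Use as denominator all older inpatients, by the trial's own age definition, who have been on the ward for at least 24 h on the audit morning. Log one yes/no per patient for a charted standardised assessment within 24 h of ward admission. This fits within the Research Manager's existing case-finding that morning and needs no identifying data.

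2. **Care-process items.** Keep the present sample. Record the number of patients identified per ward-day and the route of identification (dementia diagnosis recorded before this admission, other chart entry, Charge Nurse report), and report both by hospital and occasion. Add a sensitivity analysis in patients whose dementia diagnosis was recorded before the current admission. Describe this group as less affected by the intervention, not immune to it, since the diagnosis must still be charted or reported for the patient to enter. Say also that it does not cover delirium without dementia.

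3. **Text.** State that identification may differ by time and hospital and that the direction of any resulting bias is unknown.

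**Cost.** Some additional chart checking on audit mornings and two further fields to record; no additional staff or visits. The sensitivity analysis will be small, given the limit of eight patients per ward-day. The reported change in screening may turn out larger or smaller than under the present sampling.
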